### Data Presentation

Continuous variables will be presented as mean (SD) for normally distributed data and as median (IQR) for skewed distributions. Categorical variables will be presented as frequencies and percentages. A *P* value <.05 will be considered statistically significant. Given the pilot nature, emphasis will be placed on effect sizes and CIs rather than *P* values alone. Descriptive statistics and data analysis will be performed using Microsoft Excel - Office 365 and IBM SPSS Statistics software (version 31.0; IBM Corp).

### Data Monitoring

Data and study monitoring will be performed once 10 residents have been recruited to the pilot trial. Given the pilot nature and low-risk intervention, a formal data monitoring committee has not been established. The principal investigator will review safety data after every 5 residents. The principal investigator, the telementors, and the on-site consultant surgeon will conduct monitoring in brief meetings (telephone calls or Teams meetings) prior to the inclusion of each resident. Technical issues related to telementoring, the mentoring framework, and coaching will be addressed. Given the study’s novelty, adjustments to the telementoring framework may be necessary.

Given the pilot study’s intensive follow-up (5 procedures in 3 d), minimal missing data are expected. For the primary analysis, available-case analysis will be used. Descriptive patterns of missing data will be reported to inform the definitive RCT.

Trial monitoring will be conducted by the principal investigator. This includes a quarterly review of recruitment rates, protocol deviations, technical system performance, and adverse events. Given the single-site coordination and pilot scale, on-site monitoring visits are not planned.

### Ethical Considerations

The study was approved by the ethical committee (REK HELSE NORD 32592) and the data protection officer at Nordlandssykehuset Hospital Trust, Bodø, Norway.

All collected data were anonymized prior to analysis to ensure participant (patients and residents) confidentiality. Video recordings were deidentified and securely stored on password-protected institutional servers with access restricted to authorized personnel. Informed consent was obtained from all participants, including consent for recording and data use. The study complies with applicable data protection regulations and was approved by the relevant ethics committee and data protection authority as mentioned above.

Surgical residents will be informed that their participation is entirely optional, that there will be no repercussions if they choose to withdraw, and that they may withdraw without providing a reason. Upon signing in, all surgical residents must sign an electronic permission document and a mentee-mentor contract (intervention arm). Protocol adherence will be monitored by reviewing recorded sessions.

This educational intervention does not pose direct risks to participants beyond those inherent in standard surgical training. No specific posttrial care provisions are required. Residents receive no compensation for participation.

Patients will be asked to provide informed consent. The study group does not anticipate any ethical implications for patient participation, as the telementoring (intervention arm) will provide increased surgical expertise in the OR.

Any protocol modifications will be submitted to REK for approval before implementation. Amendments will be documented with date and rationale, communicated to investigators and the trial registry, and reported in the final publication.

### Patient and Public Involvement

This pilot study was designed without formal patient or public involvement in the research design, conduct, or reporting plans. Patients are included solely as surgical cases, with the study focusing on surgical trainee education rather than on patient-centered outcomes. Surgical residents, the primary study participants, were consulted informally during protocol development to assess the acceptability and feasibility of the telementoring intervention. For the planned definitive RCT, we will consider establishing a stakeholder advisory group, including patient representatives and surgical trainees, to inform outcome selection, dissemination strategies, and study conduct.

### Dissemination Plan

The results of this pilot study will be submitted for publication in an international peer-reviewed journal, regardless of the outcome (positive, negative, or inconclusive). Findings will be presented at relevant surgical education and telemedicine conferences. National and international conferences in 2026, focusing on the intersection of surgical education and telemedicine, which we are looking forward to participating in, include the following: (1) The Norwegian Surgeons' Annual Meeting, October 2026. Oslo, Norway; (2) AMEE Conference, August 2026, Vienna, Austria; and (3) ASiT Annual Conference, 2027.

The trial protocol and results will remain publicly accessible via ClinicalTrials.gov. If successful, we will engage with Norwegian surgical societies and health care policymakers to discuss implementation implications for rural surgical training programs.

## Results

### Preparations Before Onset of the Study

Before the trial began, all telementors and on-site consulting surgeons participated in a Lapco TT course. The configuration of the telementoring system was finalized in December 2023. All residents, consulting surgeons, and telementors were instructed on the setup and use of the telementoring system.

### Current Study Status and Timeline

#### Completed Activities

The project initiated its operations by configuring the telementoring system across all study sites by December 2023. Following this, all mentors received Lapco TT training in February 2024. Ethics approval was subsequently secured from the Regional Committee for Medical and Health Research Ethics (REK nord 32592) on October 23, 2023, and the most recent update of the trial was registered in ClinicalTrials.gov (NCT06421584) on December 8, 2024.

#### Recruitment Status

Recruitment commenced in the Spring of 2024. Initially, the MedPresence platform was used for the first 5 resident inclusions. Due to changes in the Olympus portfolio of telementoring systems and global partnership agreement with Proximie, a platform transition to Proximie occurred in July/August 202. This included training telementors on the new system in August 2025. By December 2025, 3 residents had been included using the new platform. The remaining recruitment is scheduled to start in February 2026.

#### Anticipated Timeline of the Pilot

The project anticipates completing all recruitment by May 2026, with data collection concluding in September 2026. The data analysis phase is slated for November 2026, and the manuscript submission for the final results is expected in January 2027.

## Discussion

### Principal Findings and Interpretation

We acknowledge that telementoring is often positioned as an alternative when on-site expertise is unavailable, and the intuitive assumption is that physical presence should be superior. However, our superiority hypothesis is based on several theoretical considerations.

First, telementoring may enhance the quality of verbal instruction. When the mentor cannot physically intervene, communication must be more precise and explicit, potentially improving the teaching dialog. The structured communication required by telementoring (stop-identify-explain-instruct-check-judge) enforces a pedagogical framework that may be applied less rigorously when mentors can simply take over the instruments.

Second, the mandatory structured postoperative coaching in the telementoring arm (using the GROW model) represents an educational enhancement not typically provided in traditional training. This combination of real-time guidance and systematic reflection may amplify learning beyond that achieved through informal feedback.

Third, the telementor maintains the identical visual perspective as the operating resident without competing for the operative field or camera control, potentially allowing for more focused observational teaching.

We acknowledge, however, that these are theoretical advantages that may not materialize in practice. The pilot study will test whether any educational benefit exists and, equally importantly, will provide data to refine or reject this hypothesis before investing in a larger definitive trial. If the pilot demonstrates no advantage—or disadvantage—for telementoring compared to on-site mentoring, this finding would itself be valuable, suggesting that telementoring can serve as an acceptable equivalent (noninferior) alternative when on-site expertise is unavailable.

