This pilot RCT aims to provide foundational data for a future full-scale trial. The study aims to evaluate whether real-time ST, combined with structured postoperative coaching, is superior to traditional on-site mentoring for developing surgical skills among surgical residents. Our primary hypothesis is that residents receiving telementoring will show a 3- to 5-point improvement in GOALS scores compared with the control group.

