## Methods

### Study Design and Setting

This study is a parallel, 2-group, assessor-blind, multicenter pilot RCT. Participating surgical residents are allocated in a 1:1 ratio to either the intervention group, which receives real-time intraoperative telementoring and postoperative coaching, or the control group, which receives traditional intraoperative mentoring. The intention-to-treat principle will be applied. The study adheres to the latest SPIRIT (Standard Protocol Items: Recommendations for Interventional Trials) 2025 statements recommended for RCT protocols, as shown in Checklist 1 [26].

The Northern Norwegian Health Care Trust comprises 11 hospitals, including 1 university hospital and 10 local hospitals. Four hospitals within the Northern Norwegian Health Care Trust were initially assessed for eligibility as study sites: Sandnessjøen, Mo i Rana, Stokmarknes, and Bodø. Following a feasibility assessment, 2 hospitals—Sandnessjøen and Mo i Rana—were selected as active study sites based on surgical volume, resident availability, geographic location for ease of patient and resident inclusion in the study, and telementoring infrastructure, including the availability of telementors and on-site mentors. Stokmarknes and Bodø were not included as active recruitment sites due to anticipated pressure from acute cases in these locations, which would affect the elective surgical plan that the telementoring project was part of. Additionally, one of the initially included telementors based in Stokmarknes had to withdraw from the study. Although the telementoring infrastructure was initially installed at these locations to support patient and resident inclusion in the study, we ultimately decided to restrict inclusion facilities to Mo i Rana and Sandnessjøen. This facilitated optimal collaboration among actively participating telementors, residents, and the project administrator, KB, who was located in Bodø. Depending on the results of this pilot study, the expansion to include Stokmarknes and Bodø in a definitive RCT will be considered.

For this pilot RCT, 2 of the local hospitals, Sandnessjøen and Mo i Rana, served as study sites. Both locations offer surgical residency training programs that provide LC training.

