### Sample Size

This pilot RCT is designed to identify challenges and unforeseen pitfalls in conducting a proper RCT. Given the novelty of the topic and the resources required for an RCT, it is necessary to conduct a pilot study to assess the feasibility of a full-scale RCT.

The full RCT is designed as a superiority trial to demonstrate the superiority of telementored resident skill acquisition in the OR compared with standard training methods. Previous investigations have shown that the SD of the GOALS score is 2.5. We hypothesize that the intervention group will demonstrate significant clinical improvement in skills, as evidenced by a 3‐ to 5-point increase in the GOALS score relative to the control group. To achieve a statistical power of 0.8, a significance level (*P* value) of <.05, and to account for an expected dropout rate of 20%, 12 residents per group are required for an RCT.

This pilot study will include 5 residents in both the experimental and control arms (n=10). Residents will be stratified into 2 groups according to the number of prior LCs.

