### Statistical Analysis

The primary analysis will compare mean GOALS scores between the intervention and control groups. An independent-samples *t* test will be used for this comparison, provided that the assumption of normality is met; if normality is violated, the nonparametric Mann-Whitney *U* test will be applied. Effect sizes will be calculated using Cohen *d* to quantify the magnitude of the difference between groups and to inform sample size estimation for a future definitive RCT.

Secondary analyses will include comparisons of NOTSS scores between the intervention and control groups using the same statistical approach as that used for the primary outcome. Within-group improvement in technical performance across the training period will be assessed by comparing GOALS scores from the first to the fifth procedure using paired *t* tests. Participant satisfaction scores will be compared between groups using the Mann-Whitney *U* test, as these data are collected on an ordinal Likert scale.

Multivariate analyses will be conducted using linear regression models to examine the association between group allocation and GOALS scores while adjusting for potential confounding factors. Group allocation (intervention vs control) will be included as the primary predictor. Covariates will be selected a priori based on theoretical relevance and will include baseline surgical experience (defined as completion of 5‐10 vs 10‐20 prior LCs), baseline GOALS score from the first procedure, year of residency training, study site (Sandnessjøen vs Mo i Rana), and indicators of procedure complexity, including intraoperative findings and operative time.

Exploratory analyses will be performed to further characterize performance development and relationships between outcomes. Learning curves across the 5 procedures will be evaluated by examining trajectories of GOALS scores using repeated-measures ANOVA or mixed effects models, depending on the data structure and model assumptions. Subgroup analyses stratified by baseline experience level will be undertaken, and correlations between GOALS and NOTSS scores will be assessed to explore the relationship between technical and nontechnical performance.

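### A null result from 5 residents per arm, with no margin set, cannot suggest that telementoring is noninferior; the pilot's Cohen d is also too imprecise to size the next trial

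*Protocol article*

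**What the plan says.** **Interpretation of a null pilot.** Discussion, Principal Findings and Interpretation, defends the superiority hypothesis and then considers a pilot that shows no advantage or disadvantage for telementoring. It calls that finding valuable, "suggesting that telementoring can serve as an acceptable equivalent (noninferior) alternative when on-site expertise is unavailable". The sentence before it says the pilot "will provide data to refine or reject this hypothesis before investing in a larger definitive trial".

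**Design.** The Sample Size section describes the full trial as a superiority trial, and the Introduction hypothesizes that "residents receiving telementoring will show a 3- to 5-point improvement in GOALS scores compared with the control group". Of the pilot it says: "This pilot study will include 5 residents in both the experimental and control arms (n=10"). No noninferiority margin, hypothesis or confidence-interval rule is stated anywhere, and the word noninferior appears only in the Discussion sentence.

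**Use of the effect size.** Statistical Analysis computes Cohen d "to quantify the magnitude of the difference between groups and to inform sample size estimation for a future definitive RCT". The numbered pilot aims in the Introduction likewise list preliminary effect sizes as a means of refining that calculation.

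**Caveats elsewhere.** Limitations accepts that the sample is too small for definitive conclusions on effectiveness. Data Presentation puts the weight on effect sizes and confidence intervals rather than on P values alone.

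**The concern.** A superiority comparison that finds no difference shows only that none was detected. To call a new training mode noninferior, one needs a margin fixed in advance and a confidence interval that lies wholly on the acceptable side of it. This plan has no margin, and at 5 per arm the interval is wide. The Discussion nonetheless attaches the noninferior reading in advance to a null result, which is a likely result in a pilot of this size. It also says the pilot can reject the hypothesis, which the same lack of precision prevents.

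What is at stake is the conclusion drawn about rural training, and the size of the definitive trial or the decision to run it.

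**Working it through.** **Inputs from the article**
- 5 residents per arm; "Participating surgical residents are allocated in a 1:1 ratio".
- "Previous investigations have shown that the SD of the GOALS score is 2.5".
- Hypothesized difference 3 to 5 points, so d = 3/2.5 = 1.2 to 5/2.5 = 2.0.
- Power 0.8, P < .05 and 20% dropout for the definitive trial.

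Assumptions: two-sided 5% level (sidedness is not stated), SD taken at resident level, other SDs tried from 1.5 to 3.0, and illustrative noninferiority margins.

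**1. The plan's own figure (12 per group)**
- Normal approximation, 3 points, two-sided: n = 2 × (2.5 × 2.80/3)² = 10.9, so 11 per group; 11/0.8 = 13.75, so 14 after dropout.
- Exact t test: 12 per group before dropout (power 80.2%); 12/0.8 = 15 after.
- One-sided at 3 points (normal approximation): 8.59, so 9; 9/0.8 = 11.25, so 12. Two-sided at 3.5 points: 8.01, so 9, again 12.

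The stated 12 is recoverable under some conventions and lies close to the others. It is not the issue here. It does show that the plan already has a basis for sizing that does not need the pilot's effect estimate.

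**2. Precision of the pilot**
- SE of the difference = 2.5 × √(2/5) = 1.58.
- 95% half-width = t(0.975, 8 df) × SE = 2.306 × 1.58 = 3.65 points.
- An observed difference of 0 gives -3.65 to +3.65.

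**3. Chance of a nonsignificant result if telementoring is truly 3 points worse**
- Noncentrality = 1.2 × √(5/2) = 1.90 on 8 df; power = 0.386; nonsignificant = 61%.
- By symmetry, a true 3-point benefit is also missed in 61% of pilots.

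| Assumed SD | 95% half-width | Nonsignificant at true -3 | Observed difference better than -1 at true -3 |
|---|---|---|---|
| 1.5 | 2.19 | 21% | 2% |
| 2.0 | 2.92 | 45% | 6% |
| 2.5 (stated) | 3.65 | 61% | 10% |
| 3.0 | 4.38 | 71% | 15% |

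The last column is the normal tail above 2/SE. The half-width equals 3 points at SD = 3/(2.306 × 0.632) = 2.06. Below that SD, an observed zero would exclude a 3-point deficit; at the stated SD it does not. With 4 per arm (20% dropout) and SD 2.5, the half-width is 4.33 and 70% of pilots miss a 3-point deficit.

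**4. What noninferiority would need**

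At SD 2.5, no true difference, 80% power and one-sided 2.5%, n per arm = 2 × (2.5 × 2.80/margin)². That gives 11, 25, 44 and 99 per arm for assumed margins of 3, 2, 1.5 and 1 points, before dropout. With 5 per arm and a 3-point margin, power is 39%.

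**5. Precision of Cohen d**
- Noncentral-t 95% intervals at 5 per arm: observed 0 gives -1.24 to 1.24; observed 1.2 gives -0.20 to 2.54; observed 2.0 gives 0.39 to 3.53.
- In 400,000 simulated pilots with true d = 1.2, the 10th to 90th percentile of observed d is 0.39 to 2.37. Taken at face value, these imply about 100 per arm down to 5 (4 per arm gives 79.7% power at d = 2.37).
- The middle half of observed d, 0.78 to 1.77, implies 27 down to 7 per arm by exact t. The size actually needed at d = 1.2 is 12.

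**The case against.** The text is hedged. The Discussion sentence is conditional and says only that the finding would suggest acceptability. Nothing in Statistical Analysis tests noninferiority. The pilot d is to inform or refine the next sample size, and the Sample Size section already builds the definitive trial on a 3- to 5-point difference. Reporting d from a pilot is not in itself an error. Limitations and Data Presentation carry suitable caution.

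Most of this stands, and it rules out three stronger readings that a reader might infer:
- *That the plan commits to declaring noninferiority.* It does not; it names that reading as a possible inference.
- *That Cohen d will be the sole basis for the next trial's size.* The article does not say so.
- *That a truly worse training mode would probably be reported as acceptable.* This would need absence of a disadvantage to mean P ≥ .05, a rule the article does not state, together with the stated SD or one near it. At a true 3-point deficit and SD 2.5, the observed difference would be better than -1 point only about 10% of the time, and zero or better about 3%. A report that follows Data Presentation would usually show the deficit with a wide interval.

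The SD could also be lower if scores are averaged over five procedures and three raters, which is why the range is shown.

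The hedges do not remove the central problem. The caveats contradict the Discussion sentence and are not carried into it, and no hedge supplies a margin.

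**Conclusion.** The point holds in limited form and should be fixed. The noninferior reading of a null pilot is wrong as written: there is no margin, the design is superiority, and at the stated SD the interval is ±3.65 points, wider than the low end of the effect the article calls clinically meaningful. A true 3-point deficit would be nonsignificant in 61% of pilots at SD 2.5 (21% to 71% for assumed SDs of 1.5 to 3.0). The same imprecision means the pilot cannot reject the hypothesis in any firm sense.

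The Cohen d point is secondary. The estimate may be reported, but it leaves the required size almost undetermined.

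These figures rest on a two-sided 5% t test, all 10 residents evaluable, and 2.5 applying to resident-level means. The point concerns wording and interpretation. Randomization, data collection and the primary test are unaffected.

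**What to change.** 1. Replace the Discussion sentence with: *A nonsignificant difference will be reported as inconclusive, with its 95% CI; no claim of equivalence or noninferiority will be made from the pilot.* If noninferiority is of interest, set and justify a margin for the definitive trial.
2. Soften the statement about rejecting the hypothesis, for example to say that the pilot will help to refine the hypothesis and judge feasibility.
3. In Statistical Analysis and in the pilot aims, keep Cohen d as a descriptive result with its CI. State that the definitive trial will be sized on a prespecified meaningful difference, for example the lower end of the 3- to 5-point range, with a cautious SD. An upper confidence limit on the pilot SD is one convention among several.

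**Cost.** A few sentences, which can be changed before the analysis scheduled for November 2026. The conclusion becomes more guarded and the definitive trial may grow. For 3 points by exact two-sided t test, SD 2.5 needs 12 evaluable per arm (12/0.8 = 15 recruited). An assumed SD of 3.0 needs 17 (17/0.8 = 21.25, so 22 recruited).

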### Anticipated Outcomes

This pilot RCT is designed to determine whether ST combined with structured postoperative coaching can enhance laparoscopic skill acquisition compared with traditional on-site mentoring. We anticipate that the structured nature of telementoring—requiring explicit verbal communication and systematic feedback—may enhance learning through increased deliberate practice and reflection. If our hypothesis is confirmed, we expect to observe a 3- to 5-point improvement in GOALS scores in the telementoring group, which would represent a clinically meaningful enhancement in surgical proficiency.

Equally important, this pilot will identify practical challenges in implementing telementoring for surgical education, including technological barriers, workflow integration issues, and participant acceptance factors that must be addressed before a definitive trial.

